**Figure 2 f2:**
[figure not shown]
Data collection schedule.

### Statistical plan analysis

We will perform descriptive statistics, using the mean and standard deviation for continuous variables that present a normal distribution, the median and interquartile ranges for continuous variables that do not present a normal distribution and proportions for categorical variables.

Differences between patients receiving V_T_ less than or equal to 8mL/kg of PBW and patients receiving greater than 8mL/kg of PBW in the first 24 hours after transition to spontaneous ventilation will be evaluated using t tests, Mann–Whitney tests or chi–square tests, according to patient characteristics and data distribution.

The prevalence of adherence to low V_T_ ventilation in spontaneous ventilation during the initial 24 hours (V_T_ less than 8mL/kg of PBW), proportion of asynchrony in the first 24 hours after the transition to spontaneous ventilation, proportion of patients who return to sedation and controlled MV in the first 24 hours or at any time after the transition to spontaneous ventilation and adherence to a low PEEP/FiO_2_ table in the first 24 hours after the transition to spontaneous ventilation will be presented, along with the respective 95% confidence intervals.

Possible barriers associated with nonadherence (V_T_ during the initial 24 hours of spontaneous ventilation less than 8mL/kg of PBW) will be analyzed using a logistic regression model.

To characterize hospital survival at 28 days based on V_T_ during the initial 24 hours of spontaneous ventilation, we will employ the Cox proportional hazards model and generate Kaplan–Meier curves. We will analyze mortality within 28 days using the V_T_ during the initial 24 hours of spontaneous ventilation and according to the incidence of asynchrony during the first 24 hours after the transition to spontaneous ventilation using mixed logistic regressions with the center treated as a random effect.

The comparison of V_T_ during the initial 24 hours of spontaneous ventilation (less than 8mL/kg of PBW versus greater than 8mL/kg) in relation to ventilator-free days within 28 days will be performed using mixed generalized regression models considering the distribution that best fits the data, incorporating center as a random effect. We constructed a conceptual causal diagram in the format of a directed acyclic graph (DAG),^(24)^ including the association between V_T_ during the first 24 hours of spontaneous ventilation and ventilator-free days at 28 days and the most relevant variables (Figure 1S - Supplementary Material): body mass index (BMI) and SAPS 3 at baseline, SOFA on the day before transition, PaO_2_/FiO_2_ at the moment of the ARF diagnosis, and PEEP, RASS, and pH one hour before transition.

All analyses will be performed using the R statistical program (R Core Team; Vienna, Austria; https://www.R-project.org), and we will consider p < 0.05 to indicate statistical significance.

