### Objectives and outcomes

The primary objectives are to estimate the prevalence of low V_T_ ventilation (V_T_ < 8mL/kg of PBW) in the first 24 hours of spontaneous ventilation in patients with hypoxemic ARF and its association with ventilator-free days on day 28. Tidal volume will be assessed five times over the first 24 hours after the transition to spontaneous ventilation to account for potential variation. To determine whether V_T_ was below or above 8 mL/kg of PBW for a given patient, we will calculate the weighted average V_T_ based on the duration of each evaluation period. Accordingly, the first assessment, collected one hour after the transition, carries a weight of 1/24, the second assessment, collected 5 hours after (and 6 hours after the transition), carries a weight of 5/24, and the third, fourth and fifth assessments, collected after 12 hours, 18 hours and 24 hours of the transition, respectively, will each carry a weight of 6/24.

The secondary objectives are to estimate the association between the rate of adherence to low V_T_ ventilation in spontaneous ventilation and survival, estimate the incidence of asynchrony in the first 24 hours after the transition to spontaneous ventilation and associated mortality, estimate the proportion of patients who returned to sedation and controlled MV in the first 24 hours or at any time after the transition to spontaneous ventilation, assess the adherence to low positive end-expiratory pressure (PEEP) by fraction of inspired oxygen (FiO_2_) table in the first 24 hours after the transition to spontaneous ventilation, and identify barriers associated with nonadherence to low V_T_ ventilation during spontaneous ventilation.

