### Follow-up

We will follow patients until hospital discharge or death within the hospital and will compute the rate of adherence to low V_T_, that is, V_T_ ≤ 8mL/kg of PBW in the first 24 hours of ventilation in spontaneous ventilation, the proportion of patients with significant asynchrony in the transition to spontaneous MV, the proportion of patients returning for sedation and controlled MV in the first 24 hours, the proportion of patients returning to sedation and controlled MV at any time during MV, the rate of adherence to a low PEEP/FiO_2_ table in the first 24 hours, 28 day hospital survival and ventilator-free days. Ventilator-free days will be calculated as the number of days alive and out of MV to day 28. Patients who die before day 28 will be considered to have zero ventilator-free days; the day of inclusion will be considered day 0; for patients who are extubated and reintubated in the first 28 days, the number of ventilator-free days will be computed as the number of days alive and out of MV from the day of the last successful extubation (> 48 hours without MV) to day 28; for tracheostomized patients, the number of ventilator-free days will be computed as the number of days alive and out of MV from the day that the patient remains disconnected from the MV for more than six consecutive hours to day 28.

The data collection schedule is shown in figure 2 and table 1S (Supplementary Material).

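### The barrier model labels as nonadherence the condition (VT below 8 mL/kg PBW) that the article elsewhere defines as adherence; a minor related point is that the 8 mL/kg boundary is worded in three ways

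*Protocol article*

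**What the plan says.** All references are to the Methods of the protocol article.

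- **Barrier model** (Statistical plan analysis): "Possible barriers associated with nonadherence (V_T_ during the initial 24 hours of spontaneous ventilation less than 8mL/kg of PBW) will be analyzed" by logistic regression. No other operational definition of the event is given for this model.
- **Prevalence** (Statistical plan analysis, the paragraph just before): "The prevalence of adherence to low V_T_ ventilation in spontaneous ventilation during the initial 24 hours (V_T_ less than 8mL/kg of PBW", to be reported with a 95% confidence interval.
- **Primary objective** (Objectives and outcomes): to "estimate the prevalence of low V_T_ ventilation (V_T_ < 8mL/kg of PBW) in the first 24 hours" of spontaneous ventilation.
- **Patient classification** (Objectives and outcomes): "To determine whether V_T_ was below or above 8 mL/kg of PBW for a given patient", a weighted average of five readings is used, with weights 1/24, 5/24, 6/24, 6/24 and 6/24.
- **Follow-up**: adherence is to "low V_T_, that is, V_T_ ≤ 8mL/kg of PBW in the first 24 hours of ventilation".
- **Group tests** (Statistical plan analysis): "patients receiving V_T_ less than or equal to 8mL/kg of PBW" are compared with those above 8.
- **Ventilator-free-days model** (Statistical plan analysis): the contrast is "less than 8mL/kg of PBW versus greater than 8mL/kg".

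Identifying barriers to low VT is the last of the secondary objectives listed under Objectives and outcomes.

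**The concern.** Two consecutive paragraphs of the analysis section attach the same condition to opposite labels: VT below 8 is adherence in the first and nonadherence in the second. Every other definition in the article puts adherence on the low side of 8, so no reading reconciles the barrier definition with the rest. This is an explicit definition stated wrongly, which is different from a detail left to a fuller plan.

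At stake is the direction of the barrier results. A factor that makes low VT harder to achieve would appear with an odds ratio below 1 and be read as protective, and a factor that helps would be read as a barrier. Reversing the outcome leaves p-values and model fit as they were, so ordinary diagnostics would not reveal the error.

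The shifting boundary is a lesser matter. The same dichotomy defines the prevalence and the exposure in the ventilator-free-days comparison, so it should be written once and identically.

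**Working it through.** **1. The article's own figures, to see whether they depend on this point.** Inputs from Sample size calculation: anticipated adherence 50%, precision 5%, loss 10%, difference 3 days, SD 9 days. The analysis section gives p < 0.05; I assume two-sided.

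- Precision: n = 1.96² × 0.5 × 0.5 / 0.05² = 384.1. With 10% added, 384 × 1.1 = 422.4, which reproduces 422.
- Power with 422 × 0.9 ≈ 380 patients: 80.3% at a prevalence of 25% or 75%, and 90.1% at 50%. This agrees with the stated minimum of 80%.

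Neither figure uses the barrier model, and neither changes with the choice between < 8 and ≤ 8.

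**2. Effect of reversing the event.** If logit P(Y = 1) = a + bx, then logit P(Y = 0) = −a − bx. Every coefficient changes sign, so each odds ratio exp(b) becomes exp(−b) = 1/exp(b).

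- An odds ratio of 2.0 becomes 1/2.0 = 0.5.
- Illustrative table, nonadherent/adherent 60/40 with the factor and 40/60 without: (60 × 60)/(40 × 40) = 2.25. Reversed: (40 × 40)/(60 × 60) = 0.44.
- Confidence limits become reciprocals and change places. The size of each test statistic, and so each p-value, is unchanged.

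**3. The cut-off, place by place.**

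| Place | Wording | A weighted VT of exactly 8 is |
|---|---|---|
| Primary objective | low = < 8 | not low |
| Patient classification rule | below or above 8 | unassigned |
| Follow-up | adherent = ≤ 8 | low |
| Group tests | ≤ 8 versus > 8 | low |
| Prevalence with confidence interval | adherent = < 8 | not low |
| Barrier model | nonadherent = < 8 | on the adherent side, if read literally |
| Ventilator-free-days model | < 8 versus > 8 | in neither group |

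**4. How many patients could sit on the boundary.** The article gives no distribution of VT. Assumption: weighted VT is normal with mean m of 7 to 9 and SD s of 1 to 2 mL/kg. If values are rounded to 0.1, the share recorded as 8.0 is Φ((8.05 − m)/s) − Φ((7.95 − m)/s).

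- Largest (m = 8, s = 1): 3.99%, or 0.0399 × 422 = 16.8 patients.
- Smallest (m = 7 or 9, s = 2): 1.76%, or 0.0176 × 422 = 7.4 patients.
- Rounded to 0.01 instead: about 0.2% to 0.4%, or 1 to 2 patients.
- Unrounded: close to none, because a weighted mean of five readings divided by a height-based PBW is almost continuous.

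**The case against.** The best defence is that the intended direction can be recovered. The sentence speaks of barriers and of nonadherence, and the secondary objective does the same, so a careful analyst would code the high-VT group as the event and treat the bracket as a slip. Even if it were coded literally, taking reciprocals would restore the results, and only a secondary objective is involved. All of this stands, and it limits the seriousness. It does not remove the point, because the bracket is the only operational definition of the event and it is wrong as written.

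Four stronger readings are tempting, and the article does not support them:

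- **The odds ratios will be reversed.** This follows only if the bracket is coded literally, against the noun it explains.
- **A VT of 8 belongs to no group.** This is true of the ventilator-free-days contrast and of the below-or-above phrase in the classification rule. Elsewhere 8 is assigned: to the low group in Follow-up and the group tests, and outside it in the primary objective and the prevalence analysis.
- **Denominators differ from table to table.** Moving between < 8 and ≤ 8 shifts a patient from one group to the other and leaves the total unchanged. Only the ventilator-free-days contrast, taken literally, drops anyone.
- **The article has already settled on ≤ 8.** The ≤ 8 in the Abstract describes protective ventilation in general. The 4 to 8 range in the Discussion is compatible with ≤ 8, but the stated primary objective uses < 8, so adopting ≤ 8 would override it and should be declared as doing so.

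**Conclusion.** The point holds as a definitional error in the barrier model. The stated event is the article's own definition of adherence, and literal coding would give reciprocal odds ratios with the same p-values for a named secondary objective. Because it changes the definition of an analysis outcome it is more than a typographical matter, and it should be corrected before the model is run.

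The inconsistent boundary is real but minor. It touches the wording of both primary outcomes, yet its numerical effect is close to nil for unrounded values. The figure of about 7 to 17 of 422 patients arises only with rounding to 0.1 mL/kg and under the assumed normal distribution. The sample size and power statements are unaffected by either part.

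**What to change.** 1. Choose one analysis cut-off for low VT, apply it to the unrounded weighted average, and use it identically in Objectives and outcomes (primary objective and classification rule), Follow-up, and every paragraph of Statistical plan analysis, including the ventilator-free-days model.
2. Define nonadherence in the barrier model as the exact complement: above 8 mL/kg PBW if adherence is ≤ 8, or 8 and above if the primary objective's < 8 is kept. State that this is the modelled event, so that an odds ratio above 1 marks a barrier.
3. If ≤ 8 is chosen, say that it replaces the < 8 of the primary objective.

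The cost is wording only: no new data and no change to the sample size. It is best recorded as a dated clarification before the analysis, so that neither the boundary nor the coding is settled after the results are seen.

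### The barrier logistic model and the Cox survival model are specified without a centre effect, although the mortality and ventilator-free-days models beside them include one

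*Protocol article*

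**What the plan says.** The section on the statistical analysis plan (protocol article, Methods) names a type of model for each regression:

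- **Barriers to low tidal volume:** these "will be analyzed using a logistic regression model". Centre is not mentioned.
- **28-day hospital survival by tidal volume:** "we will employ the Cox proportional hazards model and generate Kaplan–Meier curves". No frailty, stratification or clustered variance is mentioned.
- **28-day mortality by tidal volume and by asynchrony:** analysed "using mixed logistic regressions with the center treated as a random effect".
- **Ventilator-free days by tidal volume:** "mixed generalized regression models considering the distribution that best fits the data, incorporating center as a random effect".

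The significance rule is common to all of them: "we will consider p < 0.05 to indicate statistical significance". The study design section describes recruitment through ICUs in ten Latin American countries. The article does not give the number of ICUs, the patients expected per ICU, or an ICC.

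**The concern.** Two of the four regressions allow for clustering by centre and two do not, and no reason is given for the difference. Because the text separates mixed from ordinary models in neighbouring sentences, an analyst following it would fit the barrier and Cox models as if all patients were independent.

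The barrier model is where this matters most. Its outcome is tidal volume practice, which plausibly depends on local habits and training. The Discussion itself expects regional variation in practice. If a barrier also varies between ICUs, an ordinary logistic model understates its standard error, and the barrier will be called significant too often.

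For survival, the same exposure and the same 28-day horizon are analysed twice: once with centre (mixed logistic) and once without (Cox). If the two disagree, a reader cannot tell whether the cause is the time-to-event scale or the treatment of centre.

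**Working it through.** **The plan's own figure.** The sample size does not depend on this point, and it reproduces. n = 1.96² × 0.5 × 0.5 / 0.05² = 384.2, and 384.2 × 1.1 = 422.6, against the stated 422. Nothing below changes it.

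**Inputs.** The significance level is 0.05 (from the plan; two-sided is assumed). Patients per ICU (m) and the ICC are not in the document. The values m = 10 and 20 and ICC = 0.05 and 0.10 are assumptions, chosen to show a range.

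**Step 1: design-effect formula, for a covariate that is constant within each ICU.** This is the worst case.

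Design effect: DE = 1 + (m − 1) × ICC.
True SE divided by naive SE = √DE.
Real type I error = 2 × [1 − Φ(1.96 / √DE)].

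| m | ICC | DE | √DE | Real type I error |
|---|---|---|---|---|
| 10 | 0.05 | 1 + 9 × 0.05 = 1.45 | 1.204 | 0.104 |
| 10 | 0.10 | 1 + 9 × 0.10 = 1.90 | 1.378 | 0.155 |
| 20 | 0.05 | 1 + 19 × 0.05 = 1.95 | 1.396 | 0.160 |
| 20 | 0.10 | 1 + 19 × 0.10 = 2.90 | 1.703 | 0.250 |

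With an ICC of only 0.01 and m = 10, DE is 1.09 and the type I error is 0.060.

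**Step 2: simulation of the ordinary logistic model under the null.** There were 42 centres of 10 patients (420, close to the planned 422), outcome ICC 0.10 on the latent logistic scale, and 1,000 runs per row. The covariate's between-centre share of variance was varied.

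| Share of covariate variance between centres | Rejection rate at nominal 0.05 |
|---|---|
| 0% (purely patient-level) | 0.039 |
| 10% | 0.060 |
| 30% | 0.073 |
| 100% (centre-level) | 0.128 |

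The Monte Carlo standard error at 0.05 is √(0.05 × 0.95 / 1000) = 0.007. The first two rows are therefore compatible with 5%. The third is about three standard errors above it, and the last is clearly inflated.

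**Step 3: reading the two together.** The inflation depends on how far the covariate itself varies between centres. The formula gives an upper bound for each assumed ICC and m. The simulated 0.128 lies below the formula's 0.155 for the same nominal ICC and m, as expected, since an ICC on the latent scale corresponds to a smaller one on the proportion scale that the formula uses.

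**Step 4: the Cox model.** No figure can be derived, because the document gives neither an event rate nor the between-centre variation in death. The finding here is the side-by-side comparison: same exposure, same horizon, centre in one model and absent from the other.

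**The case against.** Four points can be made in the plan's defence.

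- **No ICU-level barrier is named.** The data listed for collection are patient-level: severity scores, sedation, blood gases and ventilator settings. This stands, and it is why 10% to 25% cannot be read as the expected error for the barrier analysis. However, patient-level variables such as sedation or ventilator settings may still vary partly by ICU, and the simulation shows modest inflation once 30% of the variance lies between centres.
- **A mortality model that accounts for centre is already planned** for the same exposure and horizon. This also stands. The association with death does not rest on the Cox model alone, so the Cox point concerns consistency and that model's own standard errors.
- **An article is condensed.** That excuses silence on details. It is weaker where the article names the model for each analysis and mentions centre for some and not for others.
- **These are secondary analyses.** True, and it limits the weight of the point.

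A reader might also infer that the survival and mortality models are unadjusted for confounders, since the causal diagram is described as "including the association between V_T_ during the first 24 hours of spontaneous ventilation and ventilator-free days at 28 days and the most relevant variables" and its listed variables, among them "SOFA on the day before transition, PaO_2_/FiO_2_ at the moment of the ARF diagnosis, and PEEP, RASS, and pH one hour before transition", are not mentioned for death. The document does not support that reading. It leaves the covariates of those models unnamed and nowhere calls them unadjusted; an article may leave such a list to the full analysis plan. Nor does it say outright that the diagram's variables enter the ventilator-free-days model. The size of any confounding cannot be computed from what is given.

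**Conclusion.** The point holds for the treatment of centre. The barrier model and the Cox model are specified as ordinary models in a clustered, multinational cohort whose neighbouring models include centre.

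For the barrier model, a nominal 5% test has a type I error of about 10% to 25% for a purely centre-level covariate by the formula (assumed ICC 0.05 to 0.10, m 10 to 20). In simulation at ICC 0.10 and m = 10 the error is about 13% for such a covariate, 6% to 7% for a partly clustered one, and nominal for a purely patient-level one. The actual size is unknown, because the number of ICUs, the ICC and the list of barriers are not stated. It would be wrong to conclude that every p-value from these models is too small.

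For survival, the consequence is two analyses of the same question that handle centre differently for no stated reason. The conclusion does not extend to confounder adjustment.

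**What to change.** - **Barrier model:** fit a mixed logistic regression with a random intercept for centre, as in the mortality model.
- **Cox model:** account for centre by a frailty term or by centre-clustered robust standard errors, and state which one in advance. Frailty gives a centre-conditional hazard ratio and is the closer match to the mixed logistic model. Robust standard errors leave the hazard ratio unchanged and correct only its precision.

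**Cost:** a sentence in the plan and a few lines of code. Centre is already needed for the other two models, so no new data are required. Intervals will be somewhat wider for covariates that cluster by centre. In the worst case of a purely centre-level covariate, they widen by the √DE factors above (1.20 to 1.70 under the assumed values). For purely patient-level covariates little change is expected. The sample size is unaffected.

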### Sample size calculation

There are no previous studies that have estimated the rate of adherence to low V_T_ in patients with spontaneous ventilation; therefore, we used a conservative approach. To estimate the prevalence with a confidence limit of 5% precision, an anticipated adherence of 50%, and up to 10% loss to follow-up, we estimated that we need to include 422 patients. Additionally, we calculated the power to detect a 3 day difference in ventilator-free days with a standard deviation of 9 days,^(22)^ and we anticipate a statistical power of at least 80% even with a loss to follow-up rate of 10%, provided that the prevalence is between 25 and 75%.

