## DISCUSSION

The SPIRAL study was developed to describe the ventilation of patients with ARF in spontaneous ventilation, mainly with respect to the V_T_ applied in this phase. Randomized clinical trials have shown that low V_T_ and limited plateau pressure during controlled ventilation reduce mortality and ventilator-induced lung injury,^(3,7)^ and clinical practice guidelines recommend using protective ventilation, defined as a V_T_ of 4 - 8mL/kg and a plateau pressure below 30cmH_2_O.^(2,26)^ However, in spontaneous ventilation, the V_T_ varies according to the adjusted level of inspiratory assistance and the patient's inspiratory effort, which makes it difficult to control the V_T_. Previous physiological studies^(27,28)^ have shown that it is possible to maintain V_T_ below 8mL/kg of PBW in the majority of patients diagnosed with ARDS who are transitioning to spontaneous ventilation. The study's focus on adherence to low V_T_ during spontaneous ventilation reflects challenges faced by clinicians in daily practice. We chose to use a cutoff of 8mL/kg PBW instead of 6mL/kg because although most clinical randomized trials have targeted 6mL/kg PBW, V_T_ up to 8mL/kg were allowed in most studies.^(4,7)^ Additionally, clinical guidelines define protective ventilation as a V_T_ of 4 - 8 mL/kg^(2,26)^ and prior observational trials^(19)^ have used this definition.

The study's primary and secondary objectives cover a broad spectrum of clinical outcomes, including ventilator-free days, survival, incidence of asynchrony, and identification of potential barriers to adherence to low V_T_, enabling a comprehensive view of the impact of ventilation strategies on patient-centered outcomes. Data will be collected at several timepoints during the first 24 hours after the transition to spontaneous ventilation. This approach takes into account possible variations over time and will enable a differentiated understanding of V_T_ dynamics during this critical period. Due to possible variations in V_T_ with spontaneous ventilation over time, we chose to use the weighted average of V_T_ to obtain a more representative assessment of the ventilation dynamics during the first 24 hours of spontaneous ventilation.

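### The only stated tidal volume–ventilator-free days model cuts a continuous exposure at 8 mL/kg; a prespecified continuous analysis beside it would recover dose-response information and power if the relation is graded

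*Protocol article*

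**What the plan says.** Under Objectives and outcomes, the Protocol article makes two things primary: the prevalence of low VT in the first 24 hours of spontaneous ventilation, and the association of low VT with VFD at day 28. On measurement it says "Tidal volume will be assessed five times over the first 24 hours after the transition to spontaneous ventilation", and that to classify a patient "we will calculate the weighted average V_T_ based on the duration of each evaluation period". The weights are 1/24, 5/24, 6/24, 6/24 and 6/24. The exposure is therefore a continuous number before it is cut.

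Under Statistical plan analysis, the VFD comparison is VT "less than 8mL/kg of PBW versus greater than 8mL/kg", fitted by "mixed generalized regression models considering the distribution that best fits the data, incorporating center as a random effect". The unadjusted group comparisons in that section also split at 8 mL/kg. No analysis of VFD on continuous VT is stated.

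Under Sample size calculation, power is for "a 3 day difference in ventilator-free days with a standard deviation of 9 days": "we anticipate a statistical power of at least 80% even with a loss to follow-up rate of 10" per cent, "provided that the prevalence is between 25 and 75" per cent.

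The Discussion gives the reason for the threshold: "We chose to use a cutoff of 8mL/kg PBW instead of 6mL/kg", because most trials allowed values up to 8 mL/kg and because guidelines and earlier observational work use that definition.

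**The concern.** The Discussion explains why the threshold is 8 rather than 6 mL/kg. That settles what counts as adherence, which is what the prevalence objective needs. It does not explain why the association with VFD should use only the two-group version of VT. In that model a patient averaging 7.9 mL/kg and one averaging 8.1 are opposites, while patients at 8.1 and 12 are the same.

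If the relation is graded, the split gives up power on a primary objective and cannot show the shape of the relation. The exposure balance is also uncertain. The article says that no earlier study estimated adherence in spontaneous ventilation, and its Discussion cites physiological studies in which most ARDS patients could be kept below 8 mL/kg. A split outside 25–75% is therefore possible, and the stated power does not cover it.

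**Working it through.** **Inputs from the article.** Sample size 422; 10% loss; precision 5 points at 50% adherence; VFD difference 3 days; SD 9 days; prevalence 25–75%; significance level 0.05. The article does not say one- or two-sided; two-sided is assumed.

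**Step 1: reproduce the plan's figures.**
- Prevalence: n = 1.96² × 0.25 / 0.05² ≈ 384, and 384 × 1.10 = 422.4, which gives the stated 422.
- Evaluable patients: 422 × 0.90 ≈ 380.
- Binary power: noncentrality = (3/9) × √[380 p(1−p)]; power = Φ(noncentrality − 1.96).
  - p = 0.50: noncentrality 3.25, power 90.1%.
  - p = 0.25 or 0.75: noncentrality 2.81, power 80.3%.

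The claim of at least 80% holds for the binary contrast within the stated range.

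**Step 2: information kept by the cut.** For a normal exposure with a linear effect, the share kept is φ(z_p)² / [p(1−p)].

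| Split | Kept | Lost | 380 patients act like |
|---|---|---|---|
| 50/50 | 0.637 | 36.3% | 242 |
| 40/60 | 0.622 | 37.8% | 236 |
| 30/70 | 0.576 | 42.4% | 219 |
| 25/75 | 0.539 | 46.1% | 205 |
| 20/80 | 0.490 | 51.0% | 186 |
| 10/90 | 0.342 | 65.8% | 130 |

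**Step 3: sensitivity to the VT shape.** The article gives no VT distribution, so other shapes were assumed, still with a linear effect. The loss is 1 − corr(VT, cut VT)². Here p is the share of patients below the cut.

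| Assumed VT shape | p = 25% | p = 50% | p = 75% |
|---|---|---|---|
| Normal | 46% | 36% | 46% |
| Uniform | 44% | 25% | 44% |
| Lognormal, log-SD 0.25 | 57% | 40% | 39% |
| t, 5 degrees of freedom | 52% | 46% | 52% |

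The range is about 25% to 57%. If the true effect is a step at 8 mL/kg, the cut loses nothing.

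**Step 4: the same in power.** Suppose a linear relation in a normal VT produces the 3-day group difference. The continuous noncentrality is the binary one divided by √(share kept).
- 50/50: 3.25 / √0.637 = 4.07, power about 98% (binary 90%).
- 25/75: 2.81 / √0.539 = 3.83, power about 97% (binary 80%).

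The two continuous figures differ because a fixed 3-day group difference implies different slopes: 1.88 days per SD of VT at 50/50 and 1.77 at 25/75.

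**Step 5: outside the 25–75% range.**
- Group difference fixed at 3 days: binary power is 74% at 20/80, 64% at 15/85 and 50% at 10/90.
- Slope fixed at 1.88 days per SD (3 days at an even split): binary power goes from 90% at 50/50 to 66% at 10/90. The continuous term stays at 1.88 × √380 / 9 = 4.07, about 98%, wherever the cut falls.

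**The case against.** The strongest reply is that the contrast answers the question asked. The primary objective concerns low VT, defined by a threshold, and its association with VFD. The Discussion supports that threshold, and a slope per 1 mL/kg answers a different question. This stands, and is why the binary contrast should remain primary.

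A second reply is that supportive models are often left to an analysis plan or full protocol, neither of which is shown. This stands in part. What can be said is that the article states only the cut version; whether the study will analyse only that version cannot be known from it. The point is about the form the article fixes for a primary objective, not about missing detail.

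A reader might infer four stronger things that the article does not support:
- **That the study is underpowered.** It is not on its own inputs; Step 1 reproduces the stated power.
- **That the association objective fails outside 25–75% prevalence.** Power declines gradually, the article discloses the condition, and the prevalence objective is unaffected.
- **That error in the spot readings is a reason to prefer continuous VT.** Random error attenuates a slope too, averaging five weighted readings reduces it, and the Discussion acknowledges intermittent sampling as a limitation.
- **That mortality is dichotomised in the same way.** The Cox and mixed logistic models refer to VT in the first 24 hours without stating a cut, so the point is confined to VFD.

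**Conclusion.** The point holds as a worthwhile improvement to a sound analysis. The one VT–VFD model in the article uses VT split at 8 mL/kg although the continuous weighted average is in hand, and the reason given for the threshold does not extend to using only the split for the association.

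The size of the loss depends on assumptions the article cannot confirm, so 36–46% should be read as an illustration and not as a property of the plan. Every linear scenario tried within 25–75% prevalence loses at least a quarter of the information, whereas a true step at the threshold loses none. The two-group contrast alone cannot tell these situations apart; a spline could help to do so.

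**What to change.** Keep the 8 mL/kg contrast as the primary VFD analysis. Prespecify beside it, labelled supportive, the same mixed model for VFD (same covariates from the causal diagram, centre as random effect) with weighted-average VT entered as continuous:
- a linear term, reported per 1 mL/kg of predicted body weight;
- a 3-knot restricted cubic spline, to show the shape of the relation.

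Fix both forms before results are seen, so that the choice between cut and continuous cannot follow the data. If an analysis plan already contains this, a reference to it is enough.

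The cost is a little extra analysis and one more result to interpret alongside the primary contrast. No new data or patients are needed.
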